## Abstract

**Background:**

Macular neovascular diseases can cause severe vision loss. A newly approved anti—VEGF drug Conbercept has shown good efficacy and safety in rigorous random controlled trials (RCT), however, it cannot fully reflect the clinical application of Conbercept in real world clinical practice. Moreover, anti-VEGF drugs are expensive and often require multiple treatments, and some patients have poor or even no response to the drugs,this resulted enormous waste of medical resources. Therefore, how to find out those patients who have good response, and how to develop individualized therapeutic regimen in real world need to be urgently investigated in the aspect of pharmacogenomics and pharmacometabolomics.

**Methods:**

This study is a multicenter, prospective, observational study of Conbecept treating macular neovascular diseases in China. Patients suffered from age-related macular degeneration, polypoidal choroidal vasculopathy, and pathological myopia who already planned to receive Conbercept treatment will be recruited. We aimed to enroll more than 5000 patients from 43 ophthalmic centers in China. Patients’ clinical data and blood samples will be collected during the one-year follow-up period. Finally, the safety and efficacy of Conbercept, and the potential predictors of patients’ response to Conbercept will be investigated by pharmacogenomics and pharmacometabolomics analysis.

**Discussion:**

This study will provide important data of Conbercept in treating macular neovascular diseases in real world. Besides, finding the predictor of patients’ response will help doctor make more precise individualized therapeutic regimens.

**Trial registration:**

ClinicalTrials.gov, NCT03128463. Registered on 9 March 2017.

**Electronic supplementary material:**

The online version of this article (10.1186/s12886-018-0812-4) contains supplementary material, which is available to authorized users.

## Background

Macular neovascular disease characterized by subfoveal choroidal neovascularization (CNV) remains the leading cause of irreversible blindness that impacts quality of life [1–4] including age-related macular degeneration (AMD) [5], polypoidal choroidal vasculopathy (PCV) [6], pathological myopia (PM) [7, 8] and so on. Previous therapies such as photodynamic therapy with Verteporfin showed limited success [9]. Due to the similarities in pathogenesis of CNV, anti-vascular endothelial growth factor therapy (anti-VEGF) has been shown to be effective and has become the first choice for the treatment of CNV [10].

Conbercept (Lumit®, Chengdu Kanghong Biotech Co., Ltd., P. R. China) is an anti -VEGF drug developed in China in recent years. It has been approved by the China Food and Drug Regulatory Administration (CFDA) for the treatment of neovascular AMD and was recently admitted directly to the Phase III clinical trials in the U.S. Food and Drug Administration (FDA). This drug competitively prevents the binding of VEGF to its receptor and inhibits the downstream pathway activation, and has a higher binding affinity to the most potent pro-angiogenic alternative splicing of VEGF——VEGFA than other widely used anti-VEGF drugs [11, 12].

In our previous phase I and II studies, the intravitreal administration of Conbercept successfully improved visual acuity and reduced central retinal thickness and CNV area in patients with neovascular AMD. AURORA study and its subgroup analysis showed that Conbercept has good efficacy and safety in treating macular neovascular diseases such as PCV and AMD [13, 14]. After three months’ injection, average changes in BCVA in the 0.5- and 2.0-mg groups were 8.97 and 10.43 letters, respectively [14]. During the 12 months, patients have good tolerances for the repeated intravitreal injections of Conbercept [14].

Although the above clinical trial results showed that Conbercept had good efficacy and safety in treating AMD [14], the exact therapeutic regimen and the efficacy still needs to be further studied in real world. The reasons are as follows: i) Limitation of external validity of randomized controlled trials (RCTs) conducted in AMD, because they may not fully reflect the clinical application of Conbercept in real world; ii) Lack of RCT of Conbercept in the treatment of CNV secondary to PM, and the efficacy of Conbercept in PCV only resulted from subgroup analysis. Therefore, further clinical trials of Conbercept in other macular neovascular disease need to be explored, and our study may provide the preliminary evidence for further RCTs in PM and PCV; iii) Anti-VEGF therapy poses significant financial and treatment burden on patients and social insurance system due to frequent injections and visits. Moreover, some patients have poor or even no response to the drugs. It is important to find out those who have good response and develop individualized therapeutic regimen with the use of pharmacogenomics and pharmacometabolomics technologies.

Therefore, we present the design and methodology of a prospective study to investigate the efficacy and safety data of Conbercept in treating macular neovascular disease in clinical practice and explore the relationships of phenotype and the effectiveness of the Conbercept through pharmogenomics and pharmacometabolomics in China.

## Methods and analysis

### Study design and objectives

We intended to conduct a prospective observational study within multicenter to investigate the efficacy and safety of Conbercept in real world and explore the potential predictors of patients’ response to Conbercept (Protocol no. 2.0 date 20 October 2017).

This program starts from March 2017 (FPFV, First Patient First Visit) and will finish in December 2018 (LPLV, Last Patient Last Visit). We recruit eligible participants attending 43 ophthalmologic centers in China (The case report form is attached in Additional file 1). Patients are screened according to unified diagnostic standard guideline or consensus of Chinese Ocular Fundus Disease Society. Those who subject to all of criteria, we will explain our study to patients and their families. Finally, consent form will be signed if they are willing to participate in our study. Their clinical data will be collected during the five visits: baseline (V1: enrollment period, first Conbercept treatment), following 1 month (V2), following 3 month (V3), following 6 month (V4), following 12 month (V5) during the 1-year follow-up. (The clinical information collected during each visit is attached in Additional file 2) Patients whose actual visits are within 7 days before or after the registration time can be considered available. If the participants come back for visit but their visit time is beyond the time window or failed to register the clinic follow-up for some reason, the researchers should implement a registration by phone call. If the participants cannot be contacted by telephone, the visit can be considered lost. All the reasons and processes should be documented. The case report form is attached (Additional file 1).

Among subjects, 500 patients will be selected to conduct pharmacometabolomics analysis compared with 500 healthy volunteers for detecting disease-associated metabolites. After the evaluation of patients’ curative parameters (listed below), preliminary pharmacogenomics and pharmacometabolomics analysis will be carried out. We will pick up 500 patients, half of them have good response from significant effective group and half have no response from deterioration group, their blood samples will be analyzed by pharmacogenomics and pharmacometabolomics to find out response-associated predictors, and then the predictors of patients’ response to Conbercept will be further validated in all of the recruited subjects. Figure 1 is the study design flow.

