### Data collection and management

Investigators in the 43 ophthalmic centers should follow Standard Operating Procedures (SOPs) during clinical data and blood sample collection, data recording and transfer, sample storing and transfer. All of the data will be filled in the electronic case report form (CRF). At the initial visit (V1), information about the participant’s sex, age, body weight, height, vital signs, medical/surgical history, concomitant medications and eye conditions will be recorded. For ETDRS vision, eye examinations, optical coherence tomography (OCT), fluorescein fundus angiography (FFA) will be checked by clinicians who have got international unified certification. The eye conditions, treatment records, accompanying medications and adverse events are recorded by practiced clinicians at five visits. Clinical images will be uniformly transferred to Shanghai Jiaotong University Ophthalmic Reading Center and evaluated by qualified graders. The specific items are listed in Table 1.

**Table 1 Tab1:** Assessment protocol for the current study from V1 to V5

Visit of data entry	V1	V2	V3	V4	V5
Meets enrollment / exclusion criteria	X				
Month		1	3	6	12
Days		30 (± 7) days after first injection	90 (± 7) days after first injection	180 (± 7) days after first injection	360 (± 7) days after first injection
Consent form	X				
Demographic data	X				
Systemic and ocular disease history	X				
Best corrected visual acuity	X	X	X	X	X
Optical coherence tomography	X	X	X	X	X
Accompanying medication	X	X	X	X	X
Data record	X	X	X	X	X
Treatment program records		X	X	X	X
Adverse events	X	X	X	X	X

The clinical data and fundus imaging data will be uploaded to Electronic Data Capture (EDC) System called Oracle Clinical and Oracle Remote Data Capture (OC/RDC) churned out according SOPs. The EDC system has been checked by third party and meets international standard. And data from different centers will be managed together and go through logistic check. Each modification trace can be recorded to make sure the data is real and reliable.

Patients’ blood samples will be collected in coagulation-promoting tubes (8 ml) and EDTA procoagulant tubes (8 ml), and then be centrifuged for 20 min at 4000 rpm to separate serum and plasma respectively. All the samples will be send to Ophthalmic Biobank of Shanghai Jiaotong University via cold-chain logistic and then stored at − 80 °C.

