### Main outcome measures

#### Primary outcome

The primary outcome is visual changes primarily recorded as best-corrected visual acuity (BCVA) in EDTRS letters at V2, V3, V4, and V5 minus baseline vision (V1). The efficacy was graded as significantly effective (visual improvement ≥15 letters in EDTRS); effective (visual improvement ≥5 letters and < 15 letters in EDTRS); invalid (visual improvement < 5 letters and visual reduction< 5 letters in EDTRS); deterioration (visual reduction≥5 letters in EDTRS) [15]. Moreover, patients graded as significantly effective and effective that is BCVA improvement≥5 letters in EDTRS are defined as having response to Conbercept treatment and the response rate (the rate of patients graded as significantly effective and effective) will be assessed in the whole study population and in each diseases.

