### Quality control and management

We have made SOPs, videos and OC/RDC system to train all staffs involved in this study how to collect data, and deal with blood sample. The apparatus applied to our study have been certificated by CFDA. All prescribed drugs are from hospital pharmacy, and the empty bottle of Conbercept after injection will be retrieved to ensure the dosage used.

Data Management: Clinical information should be timely, accurately and completely recorded and entered into the CRF on national network of EDC, maintaining confidentiality in accordance with the local law for data protection. The electronic CRF should be consistent with the original medical records. All adverse events, concomitant medications should be documented, serious adverse events should be reported to the relevant authorities within 24 h.

Follow-up management: Follow-up should be conducted according to required time point under the rules. The investigators should enroll in local patients or patients who plan to have regular and long-term follow-up in the hospital, and the rate of lost to follow-up should be controlled below 20%. These procedures would help to minimize possible bias.

Center management: All researchers will be checked for the qualification, and then be trained to make sure they are familiar with the study protocol and will carry out the study strictly. Each center should appoint a clinical research coordinator (CRC) for quality control, making sure the CRF form timely recorded, assisting the check and inspection, drug reception, storage, distribution and checking procedures. CRC should report to PI when they found abnormal data or non-compliances to the protocol.

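### The rule for a visit outside ±7 days prescribes only a telephone call, which cannot supply BCVA or OCT, so the primary outcome can be missing for patients who attended

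*Protocol article*

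**What the plan says.** The rule stands in the protocol article under Study design and objectives, in three steps.

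- In window: "Patients whose actual visits are within 7 days before or after the registration time can be considered available".
- Out of window or not attended: if participants return and "their visit time is beyond the time window or failed to register the clinic follow-up for some reason, the researchers should implement a registration by" telephone.
- Lost: "If the participants cannot be contacted by telephone, the visit can be considered lost".

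Table 1, under Data collection and management, applies the same width at all four follow-up visits. The last is set at "360 (± 7) days after first injection".

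The primary outcome is the change in "best-corrected visual acuity (BCVA) in EDTRS letters at V2, V3, V4, and V5 minus baseline vision (V1"). Central retinal thickness at the same visits is a secondary outcome. Under Data collection and management, ETDRS vision and OCT are to be checked by certified clinicians.

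The follow-up paragraph of Quality control and management adds that "the rate of lost to follow-up should be controlled below 20" per cent.

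**The concern.** The rule puts two different situations under one instruction. A participant who did not attend can only be telephoned. A participant who attended on the wrong day can be examined, yet the only action given is again a telephone call. If sites follow the text, they forgo a BCVA and an OCT that they could have had, and no later analysis can recover a measurement that was never taken or never entered.

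The consequences go beyond the mean change in BCVA. The response grades, the response rate overall and by disease, the choice of 250 good responders and 250 deteriorated patients for the omics work, and the validation in all recruited subjects all depend on BCVA at follow-up. The study is also justified by the limited external validity of randomised trials, so losing measurements from less punctual patients works against its purpose.

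The study's own quality measure may not show the loss. The only definition of lost in the article concerns telephone contact, not whether BCVA was obtained.

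**Working it through.** The article states no figure for this point, so there is nothing to reproduce. The check has three parts.

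**1. The rule against the outcomes.**

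| Situation at a scheduled visit | Action stated | BCVA and OCT from that action | Counted as lost? |
|---|---|---|---|
| Attends within ±7 days | visit available | yes | no |
| Attends outside ±7 days | telephone registration | no | no, if reached |
| Does not attend, reached by telephone | telephone registration | no | no |
| Does not attend, not reached | none further | no | yes |

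The second row is the problem: the patient is present, the stated action yields no outcome, and the visit is not lost.

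**2. Where the windows lie.** Inputs are days 30, 90, 180 and 360 and ±7 days, from Table 1. The windows are days 23–37, 83–97, 173–187 and 353–367. The days between them number:

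- 83 − 37 − 1 = 45
- 173 − 97 − 1 = 75
- 353 − 187 − 1 = 165

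An attendance for a study visit on any of these days falls under the telephone instruction.

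**3. Illustration of size.** Let N be the number enrolled, L the share of visits lost, and q the share of reached patients who attend out of window and have no BCVA recorded. N = 5000 is the article's enrolment target (stated as more than 5000), and L = 20% is its upper limit. The range of 10% to 40% for q is an assumption, because the article gives no visit-time data. Reached non-attenders are set to zero for simplicity, since their BCVA is missing under any rule.

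Patients with BCVA = N × (1 − L) × (1 − q)

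| q | L = 0%: with BCVA (missing) | L = 20%: with BCVA (missing) |
|---|---|---|
| 10% | 4500 (10%) | 3600 (28%) |
| 20% | 4000 (20%) | 3200 (36%) |
| 30% | 3500 (30%) | 2800 (44%) |
| 40% | 3000 (40%) | 2400 (52%) |

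For example, 5000 × 0.8 × 0.7 = 2800, so 2200 of 5000 (44%) are missing. If the out-of-window BCVA is recorded and kept, the two columns become 5000 (0% missing) and 4000 (20% missing) whatever q is.

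**The case against.** The strongest reply is that the article nowhere says an out-of-window BCVA is deleted, left unentered or excluded. It prescribes a call without saying that the call replaces an examination, and its use of registration is loose enough that the call may only document the missed slot. The case report form and the list of items per visit are in additional files not shown here, and they may allow an off-schedule BCVA to be entered. This stands: discarding is an inference from the definition of an available visit and from the single action given. It does not remove the point, because a site that follows the text has no instruction to measure or keep the value.

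Four stronger readings are tempting and go beyond the documents.

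- **That the 20% limit certainly overlooks these patients.** Study design and objectives defines a lost visit. Quality control and management limits loss to follow-up without defining it by the telephone rule. The link is a reading, though the article offers no other definition. Reasons must also be documented, so telephone-only contacts should be identifiable.
- **That a third to a half of month-12 values would be lost.** With normal timing centred on target, 2 × (1 − Φ(7.5/SD)) gives 13%, 28%, 45% and 59% for SDs of 5, 7, 10 and 14 days. The distribution and the SDs are both assumed, so no value in that range can be claimed.
- **That the loss is informative because stable patients come late and worsening ones early.** This is plausible, but nothing in the article supports it.
- **That routine care sets the visit dates.** Treatment is observational, but the assessment days are fixed in Table 1. Investigators are told to enrol local patients or those planning regular follow-up, and an early attender may still be seen later inside the window. These measures should reduce out-of-window visits, by an unknown amount.

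It is also fair to say that assigning off-schedule visits to time points and modelling actual time belong to a statistical analysis plan, and their absence here is no fault. The telephone instruction is different, because it governs what is collected and the protocol itself states it.

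**Conclusion.** The point holds as a defect in a stated data-collection rule. For a participant who attends outside ±7 days, the only action given cannot yield the primary outcome or the OCT outcome, and the visit is not lost if the participant is reached. As written, the rule can therefore leave BCVA missing for patients who attended. Read with that definition of a lost visit, the 20% limit would not register this.

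The size is unknown. Under the assumed 10% to 40% of reached patients out of window, 10% to 40% of BCVA values at a visit would be missing with no visit recorded as lost, and 28% to 52% if losses also stood at the 20% limit. These figures rest on the assumed share and on no BCVA being recorded at those attendances. The documents do not establish that values are discarded, that the results would rest on unusually punctual patients, or that bias runs in a particular direction.

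**What to change.** Amend the visit rule, the standard operating procedures and the electronic data capture instructions as follows:

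1. Record BCVA, OCT and the actual date at every attended visit, whatever the day, and keep them for analysis. Use the set within ±7 days as a sensitivity analysis.
2. Reserve the telephone call for participants who do not attend.
3. Count a telephone-only contact as missing BCVA.
4. Report missing BCVA separately from lost contact, or set the 20% limit on missing BCVA.

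How off-schedule values are assigned to visits can be left to the statistical analysis plan. If the case report form already accepts them, only the sentence in the protocol needs correcting.

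No visit or procedure is added. The price is slightly more spread in assessment timing and a less favourable reported loss rate. The article reports 3055 patients recruited and recruitment still open, so an early change protects the most data.

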### Participants and recruitment

More than 5000 patients will be recruited from 43 ophthalmic centers in china that suffer from AMD, PCV, and PM (List of Ophthalmic Center in Additional file 3). And it is the first time for them to receive ocular injection of Conbercept. Doctors in outpatient clinic who diagnose and prescribe are independent of the investigators in this study. The 43 ophthalmic centers cover most regions of China. The recruitment capacity of each center will be mainly depended on the daily outpatient and registration capacity, as well as follow-up conditions. Participation is voluntary and consent is obtained before the procedures. Until now, the recruitment and primary pharmacogenomic analysis is ongoing and 3055 patients have been recruited.

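### The response-metabolite sample is picked on visual grade alone across 43 centres, with the spin set in rpm and no centre or batch term named, so centre handling could pass for response if response also varies by centre

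*Protocol article*

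**What the plan says.** Study design and objectives gives the rule for the discovery sample: "We will pick up 500 patients, half of them have good response from significant effective group and half have no response from deterioration group". No other criterion is stated. The predictors found are then to be validated in all recruited subjects.

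Participants and recruitment describes the source: "More than 5000 patients will be recruited from 43 ophthalmic centers in china". It adds that "The 43 ophthalmic centers cover most regions of China" and that "The recruitment capacity of each center will be mainly depended on the daily outpatient and registration capacity", so centres will be of unequal size.

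Data collection and management says that the blood tubes are "centrifuged for 20 min at 4000 rpm to separate serum and plasma respectively". The next sentence reads "All the samples will be send to Ophthalmic Biobank of Shanghai Jiaotong University via cold-chain logistic". Separation is thus described before shipment. No rotor, g-force or time to spin is given. The same section requires common standard operating procedures for sample collection, storing and transfer.

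Data analysis has a general provision for confounding: multivariable models, or else propensity score matching or inverse probability weighting. No covariate is named. Its separate paragraph on the omics work lists classifiers, univariate tests and regression with a cut-off of p < 0.05. Comparisons are specified by disease and by response; centre and assay batch are not mentioned.

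**The concern.** A metabolite that reflects where and how blood was handled is not a response marker. It becomes associated with response if the good-response and deterioration groups have different centre make-ups. A pick on grade alone does nothing to prevent that.

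The rpm rule leaves one source of handling difference in place even when every centre complies, because the same speed gives different forces on different rotors.

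Two usual protections are weak here. A larger discovery sample makes the artefact easier to detect, not smaller. Validation in the whole cohort uses the same centres and includes the discovery patients, so a centre artefact would tend to be confirmed. At stake is the study's aim of naming blood predictors that guide individual treatment.

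**Working it through.** **Inputs from the article.** 500 patients, 500/2 = 250 per group; more than 5000 recruited at 43 centres (5000/43 = about 116 each on average); loss to follow-up: "the rate of lost to follow-up should be controlled below 20" per cent, so about 5000 x 0.8 = 4000 evaluable at that limit; grades at a gain of at least 15 letters and a loss of at least 5. The article gives no effect size, SD or power for the 500, so there is no sample-size figure to reproduce. It also gives no response rates, centre sizes or between-centre variation. Everything below on those quantities is assumed.

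**Spin force.** RCF = 1.118 x 10^-5 x r (cm) x rpm^2. With rpm = 4000, rpm^2 = 1.6 x 10^7 and the multiplier is 178.88 per cm.
- r = 8 cm (assumed): 178.88 x 8 = 1431 x g
- r = 18 cm (assumed): 178.88 x 18 = 3220 x g

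The ratio is 18/8 = 2.25. How far this shifts any metabolite is not in the article.

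**False positives, letter-scale model.** BCVA change N(9, 13) letters with a between-centre SD as shown, 43 unequal centres, null metabolites, t test of 250 v 250 picked on grade alone, nominal 5%. The ranges for 5000 patients run over 5-30% of metabolite variance lying between centres.

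| Between-centre SD | 5000 patients | 4000 evaluable |
|---|---|---|
| 0 | not run | 4.5-5.1% |
| 2 letters | 5.3-6.8% | 5.7-7.6% |
| 3 letters | 6.1-10.9% | 6.9-15.3% (SD 3-4 together) |
| 4 letters | 6.9-17.6% | as above |

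The low ends for 5000 patients belong to the smallest handling share, 5%. With shares of 10-30%, the two runs together give about 6-8% at SD 2 and 7-18% at SD 3-4.

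**False positives, second model.** Beta-binomial response by centre, 4000 evaluable, rates 25% good and 10% deteriorated, 10-50% of metabolite variance between centres.

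| Response ICC | Pick on grade alone |
|---|---|
| 0 | 4.8-4.9% |
| 0.02 | 6.6-12.1% |
| 0.05 | 8.5-20.5% |
| 0.10 | 12.8-32.0% |
| 0.15 | 15.5-38.2% |

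Both models show that handling differences alone do no harm; a link between centre and response is also needed.

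**Remedies.** Within-centre pairs gave 4.7-5.4% in the beta-binomial runs and 4.7-5.5% in the letter-scale run with 4000 evaluable. Keeping the pick and adding a centre term gave 4.3-5.7%. In the 5000-patient run, pairs gave 5.1-6.6%. Since the centre effect cancels within a pair, the excess there is simulation error.

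**Cost of strict pairing.** Pairs = min(250, sum over centres of min(good, deteriorated)). Mean pairs kept, against the number per group without pairing (4000 evaluable, skewed centre sizes):

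| Good / deteriorated | ICC 0 | ICC 0.05 | ICC 0.15 |
|---|---|---|---|
| 25% / 15% | 250 of 250 | 250 of 250 | 250 of 250 |
| 25% / 10% | 250 of 250 | 250 of 250 | 241 of 249 |
| 25% / 7% | 250 of 250 | 238 of 243 | 201 of 231 |
| 15% / 10% | 250 of 250 | 249 of 250 | 204 of 249 |
| 30% / 5% | 200 of 201 | 193 of 196 | 163 of 187 |

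The largest mean loss at ICC 0.05 is 5/243 = 2%, and at ICC 0.15 it is 45/249 = 18%. In that last case the 5th percentile was 140 pairs. Separately, filling the deterioration group at all needs a rate of 250/5000 = 5.0%, or 250/4000 = 6.25%, with or without pairing.

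**The case against.** **Silence in a condensed article.** The full protocol and the operating procedures are not shown and may stratify the pick, fix the rotor or plan assay batches. This stands in part: a reader might infer that centre is deliberately ignored, and the article does not say so. What it does state is a selection rule with one criterion, a spin in rpm, and an omics analysis list broken down by disease and response but not by centre.

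**Local spinning and its effect are not documented.** This stands. Processing at the centres is implied by the order of the text only, and a reader who takes a metabolite shift as built in goes beyond the article. A difference in force is arithmetic; its effect on metabolites is an assumption.

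**No centre-response link is shown.** This stands as a limit on size: without the link, the error stays at about 5%. The link is plausible, because three diseases are pooled in the pick, prescribing is independent of the investigators, and regimens are expected to differ enough to be a secondary outcome. The article does not quantify it.

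**Safeguards exist.** Common procedures, certified BCVA testing, cold-chain transport, one biobank, training and a coordinator at each centre should all narrow centre differences. They do not turn rpm into a fixed force. The confounder provision could take in centre, but it is conditional and names no covariate, and the omics methods are listed separately. It also cannot help where a centre supplies patients to only one group.

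**Analysis could deal with it.** This is correct. Within-centre selection is one valid remedy, and a centre-adjusted analysis of the existing pick is another.

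**Conclusion.** The point holds conditionally. As written, the plan does not protect the metabolite discovery step from centre effects, and the planned validation would not by itself expose them. Harm needs both local processing differences and a response that varies by centre; the article implies the first and makes the second plausible, but documents neither. Under the assumed letter-scale inputs, the per-metabolite false-positive rate rises from 5% to 6-8% for modest centre variation and to 7-18% for larger variation. The beta-binomial model goes higher at its extremes.

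Three stronger readings are not supported. The article does not show that the artefact will occur. It is not established that pairing costs almost nothing, since the loss can reach about 18% of pairs where centres differ most, which is also where confounding is worst. Nor does the spin argument extend to the pharmacogenomic part: germline variants do not depend on centrifuge force.

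The change is worth making because the remedy is cheap. The pick follows the evaluation of response, and recruitment stood at 3055 of more than 5000 when the article was written.

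**What to change.** 1. Pick the good-response and deterioration groups balanced or paired within centre and disease where numbers allow, at random where a centre has more eligible patients than needed.
2. Where pairs run short, keep the pick on grade and analyse the metabolites stratified by, or adjusted for, centre. Name centre in the omics part of Data analysis in either case.
3. Keep the two response groups balanced across assay batches; pairs, where used, go in the same batch.
4. State the spin as g-force in the operating procedure for the remaining samples, and record which centre spun each sample.

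Cost: wording of the selection rule, the analysis section and the operating procedure, with no added patients or visits. Strict pairing usually loses 0-2% of pairs, and up to about 18% on average if centres differ strongly in response. In that case the centre-adjusted analysis should replace it. Samples already spun cannot be corrected by item 4, so items 1 to 3 carry the protection for them.
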